## Secondary endpoints

Criteria for meeting the study’s four secondary objectives are as follows:

- - 1. The first secondary objective comprises two evaluation criteria: 1) self-reported scores on the Postural Awareness Scale (APPENDIX 3) pre- and post-intervention, and at the start of each session; 2) variation in measures of postural balance pre- and post-intervention.
    2. The second objective also comprises two criteria: 1) self-reported scores on Cohen’s Perceived Stress questionnaire (APPENDIX 3) pre- and post-intervention, and at the start of each session; 2) variation in measures of allostatic load in saliva pre- and post-intervention (the corticotropic axis: cortisol, DHEA, oxidative stress; the autonomic nervous system: alpha amylase and chromogranin A).
    3. The evaluation criterion for the third secondary objective will be the correct prediction of the risk of fall injury by the machine learning model.
    4. The evaluation criterion for the fourth secondary objective will be the rate of fall injuries in each of the two groups (POTs *vs.* active control), in the period between the end of the study and the end of the selection course. Information about when each participant left the course will be collected from the physician responsible.

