## Secondary objectives

The study has 4 secondary objectives:

1. The first is to test the mechanistic hypothesis that POTs reduce the risk of fall-related injury by improving postural awareness.
2. The second is to test the mechanistic hypothesis that POTs reduce the risk of fall injury by decreasing the intensity of the psychobiological stress response during physical activities in the military context.
3. The third is to use machine learning techniques to develop a predictive model of the risk of fall injury, based on a clinical test (BESS) and paraclinical (posturography) measurements taken before physical activities begin.
4. The fourth is to evaluate the persistence over time of the effectiveness of a POT intervention in reducing the risk of fall injury. The assessment will be based on participants who continue to engage in physical activities after the end-of-study visit (and who complete the selection course); the analysis will compare the rate of fall injuries for POTs and active control groups.

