# EVALUATION CRITERIA

## Primary endpoint

The primary endpoint will be the rate of fall injuries following a loss of balance in each of the two groups (POTs *vs.* active control).

A fall injury will be recorded by the medic responsible for providing healthcare during the selection course. The injured participant will be required to attend an additional follow-up visit on the same day after the initial medical consultation.

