### Follow-up visits

A follow-up visit will be carried out just before each session of the POTs and active control interventions (the schedule for which is shown in Figure 4). During the follow-up visit, the participant will complete self-report questionnaires measuring postural awareness (the Postural Awareness Scale) and perceived stress (Cohen’s Perceived Stress).

Participants who suffer a fall trauma during the course will attend an additional follow-up visit, which will take place on the day of the injury. The military medic, or one of his or her assistants, will collect medical information relating to the trauma, and carry out a posturography measurement. The participant will then complete questionnaires measuring postural awareness (the Postural Awareness Scale) and perceived stress (Cohen’s Perceived Stress).

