## End of the study

### Discontinuation criteria for a participant

Participation will end:

- After the last session of the intervention (POTs or active control),
- On leaving the course (for whatever reason) if this occurs before the end of the intervention.

It will not be possible for a participant who leaves to re-join the program at a later date.

There are no exclusion criteria in the protocol.

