## Research schedule

- Duration of inclusion: 24 months
- Duration of the intervention: 3 weeks
- Duration of each participant’s participation: 4 weeks
- Total study time: 25 months

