# LOGISTICS

## General logistics

The coordinating investigator, with the help of her scientific collaborator, will supervise all study visits (see paragraph 6.2). For inclusion and initial evaluation visits, the coordinating investigator and her scientific collaborator will be assisted by medical staff (physicians, nurses and stretcher-bearers) in the respective military unit. Follow-up visits will be carried out prior to each intervention session (POTs or active control) by the POTs instructor. The additional follow-up visit (carried out if the participant suffers a fall trauma during the study period) and the end-of-study visit will be conducted by the unit’s medical officer or one of his or her collaborators.

The coordinating investigator will also be responsible for monitoring progress, checking that progress reports are prepared, and that Case Report Forms are updated (requests for additional information, corrections, etc.).

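### Objective 4 counts fall injuries after the end-of-study visit, but the protocol does not clearly provide for recording them in that window, and the stated durations leave it almost no time

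*Protocol*

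**What the plan says.** Under Secondary endpoints, the criterion for objective 4 is the fall-injury rate in each group "in the period between the end of the study and the end of the selection course". The same item then says: "Information about when each participant left the course will be collected from the physician responsible". Secondary objectives describes the people concerned as "participants who continue to engage in physical activities after the end-of-study visit (and who complete the selection course"). Statistical methods specifies a Cox model and a log-rank test for this comparison.

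Four places bear on how long the study observes a participant:

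- End-of-study visit: follow-up ends the day after the last session, or on the day of leaving the course if that is earlier, whatever the reason.
- Discontinuation criteria for a participant: participation ends "After the last session of the intervention (POTs or active control"), or on leaving the course if that comes first.
- Research schedule (and the Research summary): 24 months of inclusion, 3 weeks of intervention, 4 weeks per participant, and "Total study time: 25 months".
- Randomization: all participants of year Y receive the active control, and all participants of year Y+1 receive POTs.

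Three places bear on how a fall injury is recorded:

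- Primary endpoint: "A fall injury will be recorded by the medic responsible for providing healthcare during the selection course".
- Follow-up visits: "Participants who suffer a fall trauma during the course will attend an additional follow-up visit".
- General logistics: "The additional follow-up visit (carried out if the participant suffers a fall trauma during the study period") is assigned to the unit's medical officer or a collaborator.

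**The concern.** A survival analysis of objective 4 needs three things for each participant: whether a fall injury occurred after the end-of-study visit, its date, and the date at which observation stopped. The protocol names a source only for the third. Leaving the course does not identify a fall injury, because the protocol itself recognises that people leave for any reason. A candidate who is injured but stays on has no early leaving date at all.

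The injury record might fill the gap, but the protocol gives two different periods for the injury visit. Six units could read them differently. Practice could also change between year Y and year Y+1, and that change of year is the comparison between groups.

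The stated study duration adds a second problem. It appears to allow for inclusion and study participation only. Any calendar cut-off would fall on the later year, which is entirely POTs.

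At stake is whether the trial can answer its question on persistence of effect. A statistical analysis plan cannot recover injuries that were not systematically obtained.

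**Working it through.** **Step 1. Where the window lies.** The objective 4 window opens at the end-of-study visit and closes at the end of the selection course. Follow-up closes the day after the last session or on leaving the course, and participation closes after the last session. The window therefore begins where the study's own observation stops. The text schedules no visit or contact after that.

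**Step 2. What is named for the window.**

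| Needed for the Cox model | Named for objective 4 under Secondary endpoints |
| --- | --- |
| Fall injury yes/no, with cause | no source named |
| Date of fall injury | no source named |
| End of observation | date of leaving the course, from the physician |

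**Step 3. Whether the injury record covers it.**

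| Section | Period stated | Covers objective 4? |
| --- | --- | --- |
| Primary endpoint (medic's record) | the selection course | yes, on its wording, though written for the primary endpoint and tied to a same-day visit |
| Follow-up visits (injury visit) | the course | yes, on its wording |
| General logistics (injury visit) | the study period | no, if this means the three weeks |

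Study outline says that the study lasts three weeks, which supports the narrow reading of the last row. The second and third rows concern the same visit and cannot both stand for an injury after the end-of-study visit.

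**Step 4. The stated total.** One month is 30.4375 / 7 = 4.35 weeks. Inclusion plus one participation is 24 + 4/4.35 = 24.9 months, which rounds to the stated 25. The total is reproduced without any allowance for objective 4.

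**Step 5. Time left for a participant included at the end of month 24.** The study closes 4.35 weeks later.

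- Counting from the end of the 3-week intervention: 4.35 − 3 = 1.35 weeks.
- Counting from the end of the 4-week participation: 4.35 − 4 = 0.35 weeks.

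**Step 6. Share of POTs intakes cut short.** Course length is not given, so this is a range under four assumptions: a course of L weeks from inclusion, even intake, inclusion up to month 24, and collection stopping at month 25. The intakes affected are those in the last L − 4.35 weeks of a year of 12 × 4.35 = 52.2 weeks, so the share is (L − 4.35) / 52.2.

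| Assumed L (weeks) | Affected weeks of intake | Share of POTs year |
| --- | --- | --- |
| 4 | 0 | 0% |
| 6 | 1.65 | 3% |
| 8 | 3.65 | 7% |
| 12 | 7.65 | 15% |
| 20 | 15.65 | 30% |
| 26 | 21.65 | 41% |

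The last control intake is at month 12 and has 13 months before month 25, so the control share is 0% in every row.

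**The case against.** The strongest reply is that the medic's record already covers the need. Primary endpoint has fall injuries recorded during the selection course with no three-week limit, Follow-up visits uses the same period, and footnote 2 fixes the meaning of fall injury for the whole document. On this reading the leaving date is simply the censoring time that a Cox model needs alongside the medic's record. General logistics only assigns tasks, and objective 4 does not need the posturography or questionnaires of the injury visit. Placing the window after the end of the study also suggests that later collection through the physician is intended. The visit table and the schedule figure are not available to check.

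Much of this stands, and it rules out two readings that a reader might be tempted to make:

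- That the outcome is not captured at all. The Primary endpoint wording could cover it.
- That the comparison would rest on course exits. The criterion is the rate of fall injuries, and no section makes leaving the event.

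What the reply does not remove is the contradiction. The course-long wording sits under another endpoint and is tied to a study visit that General logistics restricts. Participation is declared over before the window opens, and no sentence carries injury collection into it.

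On the calendar, the reply is that truncation rests on conditions the protocol does not state, and that a Cox model treats an administrative cut-off as censoring. That is right: the cost is lost and unequal follow-up, not automatic bias. A crude comparison of proportions would be affected, because the group observed for less time has less time to accrue injuries.

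**Conclusion.** The point holds in a limited form. The protocol sets an outcome in a window that its own follow-up, participation and duration statements exclude. It names only a censoring time for that window and contradicts itself on whether a later fall triggers the injury visit. These conclusions rest on the text alone.

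The loss of late POTs follow-up is conditional. It requires courses longer than about 4.35 weeks from inclusion, intake up to month 24, and collection that stops at month 25. Objective 4 implies that courses outlast the study visits, but the protocol does not say by how much. The affected share of the POTs year runs from 0% for a 4-week course, through about 15% for 12 weeks, to about 41% for 26 weeks, with none in the control year. A reader might go further and infer that the last intake has no objective 4 follow-up, or that late POTs intakes are certainly cut short. The stated durations do not support either: a short remainder of 0.35 to 1.35 weeks exists, and the 4-week case loses nothing.

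Only the fourth secondary objective is affected; the primary endpoint is not. The change should still be made, because the gap lies in data collection and cannot be repaired at analysis.

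**What to change.** 1. Under Secondary endpoints, objective 4: have the course physician supply, for every included participant in both years, the date and cause of each fall injury up to the end of the course. Use the recording rule under Primary endpoint and the definition in footnote 2. Obtain the leaving date and the reason for leaving on the same form, and state that observation is censored at leaving or at course end.
2. Reconcile Follow-up visits and General logistics so that both give the same period for the injury visit.
3. In the Research summary and Research schedule, restate the duration of participation and the total study time so that they cover follow-up to the end of the last course, and align the end-of-participation wording with this.

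The cost is one extra form from a physician who is already asked for the leaving date, and a stated study duration longer by the remainder of the last course. The sample size does not change.

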# STUDY SCHEDULE

As the study unfolds, participants will be contacted at the following locations:

All measurements will be carried out on the premises of the respective military unit (the location of the selection course). Inclusion, and the end-of-study visit will be carried out at the respective military unit’s medical center. Both follow-up visits and POTs or active control sessions will be held at the same location as the selection course.

## Summary of patient follow-up

**Table 1 –** Summary of study visits.

[figure not shown]

## Study visit schedule

The day before the start of the selection course, candidates will receive a group briefing from the investigator or one of his or her collaborators, together with a letter informing them about the study. Candidates will be given several hours to reflect on whether they would like to participate before the inclusion visit.

### Inclusion visit

The inclusion visit will take place the day after the group information session, and before any examinations related to the study. During the visit, the investigator or one of his or her collaborators will ask the participant if they want to take part in the study, and will inform him or her:

- of the objective of the study, and any constraints,
- foreseeable risks and expected benefits,
- that personal data collected during the study will be held and processed digitally, and state his/her rights regarding access, opposition and rectification,
- that samples will be conserved for scientific purposes after the study has ended, and obtain consent.

The investigator, or a colleague will answer any questions the participant may have. The latter will then have 15 minutes to reflect on his or her decision to take part in the study. Formal agreement will be obtained by signing the consent document (three copies).

Any changes to the study that impact either patient care, or benefits, risks and constraints will be presented in a new information document. The same procedure will be used to inform those concerned.

The various copies of the information document and the consent form will then be distributed as follows:

- A copy of the information document and the signed consent form will be given to the participant.
- The original will be held by the investigating medic in a safe place that cannot be accessed by third parties.

A copy of each consent form will be sent to the sponsor or its representative after inclusion or, at the latest, at the end of the study, in accordance with the procedures communicated.

### Initial evaluation visit

The initial evaluation visit will take place immediately after the inclusion visit for subjects who have given consent to participate. During this visit, the investigator, or one of his or her collaborators, will collect clinical data (age, height, weight and gender), run the BESS, and collect posturography measurements. The participant will then complete a medico-demographic questionnaire, together with questionnaires to measure postural awareness (the Postural Awareness Scale) and perceived stress (Cohen’s Perceived Stress questionnaire). Finally, a 4 ml saliva sample will be collected.

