| Schedule | The study will consist of the following visits:   - 1 inclusion visit: inclusion interview and written consent - 1 initial assessment visit: self-report questionnaires (medico-biographical, postural awareness (Postural Awareness Scale) and stress (Cohen’s Perceived Stress Scale), clinical and paraclinical posture measurements and saliva collection. - 4 follow-up visits carried out at the start of the POT or active control sessions, consisting of: self-report questionnaires (postural awareness and perceived stress), - there will be 1 additional visit for participants who suffer a fall-related trauma during the course. The participant will complete questionnaires measuring postural awareness and perceived stress, and a posturography measurement will be performed. - 1 end-of-study visit will take place on the day following the last session of the POT or the active control, or on the day of the fall injury if it occurs before the end of the POT or active control intervention. This visit will include: paraclinical measurement of posture, self-report questionnaires (postural awareness and perceived stress) and saliva collection. |
| Number of subjects | The sample should include 200 participants in each of the two groups (POT and active control), making a total of 400 participants. |

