### End-of-study visit

Participant follow-up will end either: (*i*) on the day following the last session of the POTs or the active control intervention; or (*ii*) the day they leave the course (for whatever reason), if this occurs before the end of the intervention (POTs or active control).

A posturography measurement will be performed by the military medic, or one of his or her assistants, and the participant will complete questionnaires measuring postural awareness (the Postural Awareness Scale) and perceived stress (Cohen’s Perceived Stress). Finally, a 4 ml saliva sample will be collected.

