### Para-clinical parameters

Postural balance will be measured by a clinical test (the BESS) and posturography.

1. The Balance Error Scoring System (BESS)

The BESS assesses static postural balance (eyes closed) in six conditions, using three positions (double leg stance *vs.* single leg stance *vs.* tandem stance) on two surfaces (firm *vs.* soft) (Figure 5). The participant must remain balanced without moving for 20 seconds. Points are given for postural errors (e.g., eye opening, hip flexion greater than 30°, etc.). The sum of the points obtained in the six conditions gives the total BESS score (Docherty et al., 2006)

 
[figure not shown]

**Figure 5 –** The Balance Error Scoring System is a clinical test that assesses static postural balance in six conditions, using three positions (double leg stance *vs.* single leg stance *vs.* tandem stance) on two surfaces (firm *vs.* soft).

1. Posturography

Posturography is the recording of static postural balance using a stabilometric platform (FEETEST 6^©^, Techno Concept^®^, France) (Figure 6). It consists of four small platforms that locate the position of the body’s center of pressure from the coordinates of four points of contact (left heel, left metatarsal, right heel and right metatarsal). Postural recording takes place with eyes closed, and lasts approximately one.

[figure not shown]

**Figure 6** – The FEETEST 6^©^ platform (Techno Concept^®^).

To ensure reproducibility in measurements of para-clinical parameters, investigators from the units involved in the initial assessment visit will be trained in how to carry out the BESS test (using a video). Similarly, a standard procedure will be put in place for posturography measurements.

1. Psychometric data

Self-report questionnaires will be used to measure postural awareness (the Postural Awareness Scale) and perceived stress (Cohen’s Perceived Stress Scale).

- 1. The Postural Awareness Scale (Cramer, Mehling, Saha, Dobos, & Lauche, 2018)

This questionnaire evaluates body awareness involved in postural control. A French version is currently being validated. The questionnaire is made up of 12 items, each rated from 1 (not at all true about me) to 7 (very true about me). The questionnaire assesses two dimensions of postural awareness: (*i*) Ease/Familiarity with Postural Awareness; and (*ii*) Need for Attention Regulation with Postural Awareness.

- 1. Cohen’s Perceived Stress Scale (Cohen, Kamarck, & Mermelstein, 1983)

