**Analysis of secondary objectives**

For the first secondary objective, the effect of the POTs intervention on postural awareness will be evaluated by comparing the following for the POTs group: (*i*) scores on the Postural Awareness Scale at the six measurement times (repeated measures ANOVA), and (*ii*) posturography measurements pre- and post-intervention (paired samples comparison of means).

For the second secondary objective, the effect of the POTs intervention on the psychobiological stress response will be evaluated by comparing the following measures for the POTs group at all six measurement times: (*i*) scores on Cohen’s Perceived Stress Questionnaire (repeated measures ANOVA), and (*ii*) biological stress variables (paired samples comparison of means).

For the third secondary objective, machine learning will be used to evaluate the accuracy of the predictive model of the risk of fall injury using the following calculation:

|  | $\text{Accuracy=}\frac{\text{True }\text{Fall-related injury }\text{participants + True }\text{Non-fall }\text{participants}}{\text{Total number of participants}}$ |  |
| --- | --- | --- |

where N_prediction of trauma_ is the number of participants for whom the machine learning model predicts the occurrence of a fall injury and who do, in fact, suffer a fall injury during the selection course; N_prediction of_ _good health_ is the number of participants for whom the model predicts the non-occurrence of a fall injury and who do not, in fact, suffer a fall injury during the selection course; and N_total_ is the total number of participants included in the study.

For the fourth secondary objective, the long-term effectiveness of the POTs intervention in preventing fall injuries between the end of the study and the end of the selection course will be evaluated using a comparative survival analysis (the Cox model). Survival curves for POTs and active control groups will be compared using the log-rank test.

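### The BESS is run before repeated measures at the initial visit and at no later visit, and the POTs-only pre/post tests of objectives 1 and 2 cannot separate any carry-over from change due to POTs (minor; free to fix)

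*Protocol*

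**What the plan says.** **Initial visit** (Protocol, Initial evaluation visit). The investigator or a collaborator "will collect clinical data (age, height, weight and gender), run the BESS, and collect posturography measurements". Next, "The participant will then complete a medico-demographic questionnaire, together with questionnaires to measure postural awareness" and perceived stress. The visit closes with saliva: "Finally, a 4 ml saliva sample will be collected".

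**Follow-up visits** (Protocol, Follow-up visits). Before each session there are questionnaires only: "During the follow-up visit, the participant will complete self-report questionnaires measuring postural awareness (the Postural Awareness Scale) and perceived stress". A participant who is injured in a fall has an extra visit with posturography and the questionnaires, again without the BESS.

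**End-of-study visit** (Protocol, End-of-study visit). "A posturography measurement will be performed by the military medic, or one of his or her assistants, and the participant will complete questionnaires", and saliva is again last. The Schedule row of the Research Summary agrees on content: "This visit will include: paraclinical measurement of posture, self-report questionnaires (postural awareness and perceived stress) and saliva collection". Neither mentions the BESS, and the Figure 4 caption shows it at V1 only.

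**The tests themselves** (Protocol, Para-clinical parameters). "The BESS assesses static postural balance (eyes closed) in six conditions, using three positions" on two surfaces, held for 20 seconds each and scored for errors. Posturography is also a static eyes-closed recording.

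**Analysis** (Protocol, Analysis of secondary objectives, and the Research Summary). Objectives 1 and 2 are assessed in the POTs group only: repeated-measures ANOVA over six times for the two scales, "posturography measurements pre- and post-intervention (paired samples comparison of means") for balance, and a paired comparison for the salivary markers.

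**The concern.** A pre/post comparison within one group reads as a treatment effect only if the two measurements are made under the same conditions. Here one procedure, the BESS, stands before several baseline measures and before none of the later ones.

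A carry-over is plausible on the protocol's own account. One BESS condition, double-leg stance on a firm surface with eyes closed, is close to the posturography task, so practice or fatigue could carry over. The background section ties postural awareness to the attention a person gives to bodily signals. An error-scored posture test directs attention there shortly before the baseline Postural Awareness Scale is filled in.

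Control participants go through the same asymmetry, but they do not enter the planned tests of objectives 1 and 2, so it cannot be subtracted. What is at stake is the reading of the two mechanistic objectives.

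**Working it through.** **1. Order of measures, section by section**

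| Place in the Protocol | Initial visit | End-of-study visit |
|---|---|---|
| Research Summary, Schedule | questionnaires, posture measurements (clinical and paraclinical), saliva | posturography, questionnaires, saliva |
| Figure 4 caption | saliva, posturography, BESS | saliva, posturography |
| Initial evaluation visit / End-of-study visit | BESS, posturography, questionnaires, saliva | posturography, questionnaires, saliva |

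How firm each step is:
- The questionnaires after the BESS, and saliva last, rest on explicit sequence words in the Initial evaluation visit section.
- BESS before posturography rests on the order of a list. No sequence word stands between the two.
- Posturography before the questionnaires at the end-of-study visit is also list order. Saliva last is explicit there too.
- The absence of the BESS after baseline is consistent in all places.

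The three listings of the initial visit do not agree.

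**2. Exposure.** 6 conditions × 20 s = 120 s of eyes-closed stance, within a test that the background section puts at about five minutes.

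**3. Number of participants.** The plan's 200 per group comes from 50% against 35%, two-sided 5%, power 80%. With p̄ = 0.425:

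n = [1.96·√(2·0.425·0.575) + 0.8416·√(0.5·0.5 + 0.35·0.65)]² / 0.15² = 169.3, so 170.

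With continuity correction this is 183. Allowing 10% drop-out, 183/0.9 gives 204 and 183 × 1.10 gives 202, both close to the stated 200. Below, n = 200 × 0.9 = 180 POTs participants.

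**4. Sensitivity of the paired test.** The documents give no size for a BESS effect, so the shift d (in SD of the pre/post differences) is assumed. With no POTs effect, the two-sided 5% paired t-test has noncentrality d·√180:

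| d | noncentrality | probability of a significant result |
|---|---|---|
| 0 | 0 | 5% |
| 0.05 | 0.671 | 10% |
| 0.10 | 1.342 | 27% |
| 0.15 | 2.012 | 52% |
| 0.20 | 2.683 | 76% |

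**5. Sensitivity of the ANOVA.** Six times, only the baseline mean shifted by d, constant correlation ρ between times: λ = 180·d²·(1 − 1/6)/(1 − ρ), F with 5 and 895 degrees of freedom. ρ is not in the documents.

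| ρ | d = 0.10 total SD | d = 0.20 total SD |
|---|---|---|
| 0.3 | λ = 2.14, 17% | λ = 8.57, 60% |
| 0.6 | λ = 3.75, 27% | λ = 15.0, 86% |

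If d is instead expressed in within-subject SD, the rates are 13% and 43%. All of these take 180 people with all six ratings, which is optimistic because follow-up stops when a participant leaves the course.

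**6. Between-group comparison.** In 10,000 simulated studies with 180 per group and the same shift of 0.20 SD in both groups, a comparison of change between groups was significant in 5.05%, against 76% for the within-group test. A shift common to both groups cancels.

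**The case against.** The strongest case against has five parts.

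- **The lists may describe content, not order.** The Figure 4 caption names the BESS last, Table 1 is not visible in the text at hand, and a standard procedure for posturography is promised. This stands for BESS against posturography, which the document does not firmly fix. It does not stand for the questionnaires and saliva, where the visit section uses sequence words.
- **The contrast is small.** As listed, the end-of-study questionnaires also follow a posture recording, and saliva is last at both visits. The BESS lasts about five minutes, and the questionnaires separate it from the saliva sample. This stands. It also means that shifting baseline alone in the ANOVA simplifies the real pattern.
- **The rejection rates are not evidence.** They are power curves at assumed shifts and would look the same for a shift from any cause; the ANOVA figures also depend on ρ. This stands. They show how sensitive the planned tests are, not how large the carry-over is.
- **A reader might infer that these tests contain an order artefact that will be credited to POTs.** The documents do not support that. Nothing in them shows that the BESS alters any later measure. The direction is also open: fatigue would worsen baseline and mimic a benefit, while practice would improve baseline and hide one.
- **The larger weakness is the POTs-only analysis.** It also confounds POTs with three weeks of a selection course and with repeated testing. This is correct, and reordering leaves it in place. The BESS asymmetry differs in that the visit schedule creates it and can remove it.

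**Conclusion.** The point holds as a minor one. The initial and end-of-study sequences differ by a balance test, and the analysis planned for objectives 1 and 2 has no means of separating its effect from change due to POTs. For the two scales and saliva the asymmetry follows from explicit wording; for posturography it depends on reading a list as a sequence. The bias, if there is one, could go either way.

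Its size is unknown. Over an assumed range of 0.05 to 0.20 SD of the differences, with 180 participants and no POTs effect, the paired tests would be significant in 10% to 76% of studies. These figures are conditional on the assumed shift and are not an estimate of it. The primary endpoint, its Cox analysis and the sample size are untouched.

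**What to change.** Reconcile the Schedule row of the Research Summary, the Figure 4 caption, and the Initial evaluation visit and End-of-study visit sections to one stated sequence. Take the measures that are repeated (saliva, the two scales, posturography) in the same order at both visits, and run the BESS last at the initial visit. The order among the repeated measures matters less than its being the same; placing the scales before posturography would also match the routine follow-up visits.

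Nothing is lost by moving the BESS, since it serves as a baseline predictor for objective 3 and need only be done before the physical activities begin. The cost is a wording change before the first inclusion, with no added test, staff or time.

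This does not deal with the other time effects in the POTs-only analysis. Comparing change between POTs and active control would also cancel an order effect common to both groups, using data already collected.
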